#### Provisions for post-trial care {30}

There will be no provisions after this trial.

### Outcomes {12}

All primary and secondary outcomes will be measured at study visits at three time points: 0, 3 and 12 months (see also Participant timeline Fig. 3).

#### Primary outcome

Increased physical activity at work may lead to increased sitting time or fewer steps outside working hours [31]. To account for such possible compensatory effects of the intervention, *total* sitting time (minutes per week) was chosen as the primary outcome.

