### Eligibility criteria {10}

This study will focus on individuals at an increased risk for diabetes complications. Inclusion criteria are diagnosed with T2DM, aged 40–64 years, BMI ≥ 25 kg/m^2^, HbA1c 53–100 mmol/mol (7.2–11.3%) and working at least 75% in a mainly sedentary occupation (performing > 50% of duties while sitting). Exclusion criteria are pregnancy, regular high-intensity physical training more than 75 min/week, severe immobility or other obstacles to complete the protocol.

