#### Other outcomes

Occupational sitting time (minutes per week) and occupational steps (steps per week) will be evaluated in a secondary analysis.

Self-efficacy will be evaluated as an effect modifier of changes in sitting time and steps.

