#### Sedentary time and steps

Total and occupational sitting time (minutes per week) and total steps (steps per week) will be measured with a thigh-worn, activPAL3™ accelerometer (PAL Technologies Limited, Glasgow, UK). The accelerometer will be worn for 24 h per day for 7 consecutive days [22]. The device is initialized using manufacturer’s software with the default settings (i.e. 20 Hz, 10 s minimum sitting-upright period) and will be covered in a nitrile sleeve and fully wrapped in waterproof dressing to allow participants to wear the device during bathing activities. Participants will keep a diary on their working days and working hours.

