### Methods in analysis to handle protocol non-adherence and any statistical methods to handle missing data {20c}

By using a random effects mixed model, all participants with at least one valid measurement will be included in the analysis. Hence, intermittent missing is not expected to substantially bias the results. To address possible informative drop-outs, a sensitivity analysis will be performed using multiple imputation, including all available information on background characteristics and outcome. Random effects mixed model analysis will be used to handle data missing at random for any of the two follow-ups [37].

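### Occupational sitting and steps are counted per week, so they move with hours worked as well as with behaviour at work; total sitting and steps are better stated as a mean per valid day

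*Protocol article*

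**What the plan says.** Under Primary outcome, the protocol article explains that total "sitting time (minutes per week) was chosen as the primary outcome", so that compensation outside working hours is captured. Under Other outcomes, "Occupational sitting time (minutes per week) and occupational steps (steps per week) will be evaluated in a secondary analysis". The measurement section repeats the weekly unit: "Total and occupational sitting time (minutes per week) and total steps (steps per week) will be measured". On wear, "The accelerometer will be worn for 24 h per day for 7 consecutive days". On work, "Participants will keep a diary on their working days and working hours"; no sentence links this diary to the scaling of any outcome.

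Four other places bear on the point:

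- Objectives {7} hypothesises that the intervention will reduce sick leave, and Secondary outcome lists the number of sick leave days.
- Eligibility criteria {10} admits people "working at least 75% in a mainly sedentary occupation", so contracted hours vary.
- Sample size {14} works in steps per day, not per week.
- Section {20c} on non-adherence and missing data says that "all participants with at least one valid measurement will be included in the analysis". Some validity rule is therefore presupposed, though the article does not give it.

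**The concern.** Occupational sitting in minutes per week is the product of two things: how many hours the person worked in the measurement week, and what share of those hours was spent seated. The intervention aims at the second. The first can change for unrelated reasons and, on the trial's own hypothesis, may change because of treatment: less sick leave means more hours at work. Attendance is determined after randomisation, so randomisation does not balance it. An intervention that worked on both fronts could show no gain, or a loss, on the outcome closest to its mechanism. For occupational steps the same mechanism runs the other way and would flatter the intervention.

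The primary outcome raises a lesser question. If the weekly total is taken as a plain sum over the days recorded, each lost day removes one seventh of it. For sitting, that looks like improvement.

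**Working it through.** **Inputs from the protocol article.** Sample size {14}: 1496 steps/day, SD 2930, 15% dropout, 80% power, 142 participants, and 15–25 min of daily walking as the important difference. Statistical methods {20a}: p < 0.05, taken here as two-sided. Intervention description {11a}: interruptions building up to 3 min in every 30 min.

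**Assumptions (not in the article).** An 8-hour workday, 50–90% seated; a 5-day week; 8–11 h of sitting per day; 4000–8000 steps per day.

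**1. The plan's own figure.** Per arm, n = 2 × [2930 × (1.96 + 0.84) / 1496]² = 60.2. Allowing for dropout, 60.2 / 0.85 = 70.8, so 71 per arm and 142 in total. The stated figure reproduces.

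**2. Does the unit affect it?** Per day, 1496 / 2930 = 0.51. Per week, 10,472 / 20,510 = 0.51. A per-day unit leaves the sample size unchanged.

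**3. Yardsticks in minutes per week.** The important difference is 15 × 7 = 105 to 25 × 7 = 175. It is a whole-day walking figure and serves only as a scale, because the article gives no target for occupational sitting. The full dose of interruptions is 16 half-hours × 3 min × 5 days = 240.

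**4. Attendance and occupational sitting.**
- One extra workday adds 8 × 60 × 0.5 = 240 to 8 × 60 × 0.9 = 432 min. Against 105–175 that is 240/175 = 1.4 to 432/105 = 4.1 times. Against 240 it is 1.0 to 1.8 times.
- A between-arm difference in mean attendance of 105/432 = 0.24 to 175/240 = 0.73 workdays in the measured week would equal the yardstick.
- Illustration: three days worked at 70% seated gives 3 × 336 = 1008 min. Five days at 50% seated gives 5 × 240 = 1200 min. The weekly figure rises by 192 min although sitting per 8 hours worked fell from 336 to 240 min.

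**5. Lost wear days and total sitting, if the total is unscaled.**
- One lost day removes 480–660 min, which is 480/175 = 2.7 to 660/105 = 6.3 times the yardstick, for one person.
- To shift the contrast between arms by that amount, mean wear would have to differ by about 0.2 to 0.4 days (105/600 to 175/480).
- Equal loss in both arms adds noise. Take 60 per arm, an effect of 175 min/week, 600 min lost per day, and a fraction f of participants losing k days at each of two occasions. The added variance is 2f(1 − f)(600k)² and the effect shrinks by the factor 1 − fk/7.

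| Assumed SD of change | Full wear | 10% lose one day | 10% lose two days |
|---|---|---|---|
| 60 min/day | 63% | 49% | 29% |
| 90 min/day | 33% | 28% | 21% |
| 120 min/day | 21% | 19% | 16% |

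The entries are power. They depend heavily on the assumed SD and loss rate.

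**6. Lost wear days and steps.** One lost day is 4000/10,472 = 38% to 8000/10,472 = 76% of the planned weekly effect, so it is smaller than that effect.

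**The case against.** A reader might infer that all these outcomes are raw sums, and that lost days, time in bed and hours worked each outweigh the intervention for sitting and steps alike. The article does not support that.

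- It gives a unit, not a derivation. A daily mean multiplied by seven is also minutes per week, and the reference to a valid measurement presupposes a screening rule. Valid-day rules commonly sit in an analysis plan, and none is shown here.
- The article does not say whether the device's sitting total includes lying, so nothing can be concluded about time in bed.
- For steps, one lost day is smaller than the planned effect.
- A person's lost day is not comparable with a difference between arm means. Equal wear loss costs precision and does not bias the contrast. The waterproof dressing is there to keep the device on.
- Hours worked do not mechanically change total sitting, which covers the whole day.
- Contracts of 75% versus 100% are mostly differences between people, which randomisation balances in expectation.

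All of this stands. It can also be said that weekly occupational minutes are a legitimate exposure measure, that sick leave matters only if it falls in a week measured at 0, 3 or 12 months, and that the outcome is not the primary. These points limit the reach of the concern. They do not answer it, because no wear-validity rule removes the dependence of weekly occupational minutes on attendance.

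**Conclusion.** The point holds for occupational sitting and steps. The stated unit mixes attendance with behaviour at work, and on the trial's own hypothesis attendance may respond to treatment. As a measure of behaviour at work, weekly occupational sitting is then biased against the intervention, and occupational steps in its favour. One extra workday is 1.4 to 4.1 times the 105–175 min/week yardstick, assuming an 8-hour day that is 50–90% seated. How often leave will fall in a measured week is unknown, so the net size cannot be given. Its consequence is confined to an outcome listed under Other outcomes.

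For total sitting the point is one of precision and clarity: if the weekly figure is an unscaled sum, lost days add noise, and bias arises only if wear loss differs between arms. The article does not show that it does. The steps-per-day unit in the sample size section is a further reason to state the totals per day. None of this affects the sample size.

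**What to change.** - Define occupational sitting per 8 hours worked, or as a share of diary-recorded work time, and occupational steps per 8 hours worked. Keep the weekly totals as a descriptive or sensitivity measure.
- In the main analysis, require only some recorded work time. Do not exclude weeks for low attendance, since that conditions on a post-randomisation variable that treatment may affect.
- Define total sitting and total steps as a mean per valid wear day, and multiply by seven where a weekly figure is wanted.

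The cost is a little derivation code. The work diary is already collected and the sample size stays at 142. The drawback is that the per-hour occupational measure no longer reflects total weekly exposure, which is the reason to keep the weekly figure alongside it.

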#### Secondary outcome

Secondary outcomes are total steps, fatigue, health-related quality of life, cardiometabolic risk, number of sick leave days, medications and musculoskeletal problems.

#### Other outcomes

Occupational sitting time (minutes per week) and occupational steps (steps per week) will be evaluated in a secondary analysis.

Self-efficacy will be evaluated as an effect modifier of changes in sitting time and steps.

### Participant timeline {13}

The participant timeline for ROSEBUD trial is shown in Fig. 3.

### Sample size {14}

The sample size was calculated using data from a mHealth intervention pilot study (15 participants) [25]. To facilitate the application of the concept minimal clinically important difference (MCID), the sample size was calculated based on results for daily step counts rather than for total sitting time for which MCID has not been established in previous research. Based on an increase of 1496 (standard deviation = 2930) steps/day after 3 months, and incorporating a dropout rate of 15%, a total of 142 participants would have 80% power in finding a statistically significant difference in step count between the groups. Approximately 1500 steps/day can be translated to additional 15–25 min of daily walking (depending on walking speed) which we deem to be a minimal clinically important difference for physically inactive T2DM patients [32].

### Recruitment {15}

The recruitment strategy will include (a) personal communication at diabetes check-ups with diabetes specialist nurses, (b) written invitation and/or invitation via telephone to potential participants using local diabetes patient registers or (c) through advertisement using, e.g. posters and media adverts.

## Assignment of interventions: allocation

### Sequence generation {16a}

Participants are block randomized by a computer-generated sequence (to counteract the imbalance between the centre and skewed sex ratio) into either the intervention or the comparator arm. Randomization will be done after baseline measurements at a ratio of 1:1.

### Concealment mechanism {16b}

Participants will be randomized using REDCap (Research Electronic Data Capture), which include an online, central randomization service. Allocation concealment will be ensured, as the service will not release the randomization code until the participant has been recruited into the trial, which takes place after all baseline measurements have been completed.

### Implementation {16c}

After both participants and employers have given written informed consent. Participants are registered in REDCap (Research Electronic Data Capture). REDCap creates a study identification number for all the participants. The allocation sequence will be generated electronically in blocks to achieve a balance between the intervention and comparator arm at each study centre.

## Assignment of interventions: blinding

### Who will be blinded {17a}

Researchers responsible for statistical analysis will be blinded with regard to the group allocations. The diabetes specialist nurse and laboratory staff will not be blinded.

### Procedure for unblinding if needed {17b}

This is an open-label trial.

## Data collection and management

### Plans for assessment and collection of outcomes {18a}

#### Demographic data

Information on age, sex, country of birth, education, marital status, occupation and tasks assignment/duties, current smoking status, working hours and alcohol consumption will be self-reported. Total use of medications and eventual changes in medications will be collected from the patient records as well as a participant diary during the study period. Diabetes complications and duration as well as other chronic diseases are collected from the patient records. Participants keep diary on sick leave days during the study period.

#### Sedentary time and steps

Total and occupational sitting time (minutes per week) and total steps (steps per week) will be measured with a thigh-worn, activPAL3™ accelerometer (PAL Technologies Limited, Glasgow, UK). The accelerometer will be worn for 24 h per day for 7 consecutive days [22]. The device is initialized using manufacturer’s software with the default settings (i.e. 20 Hz, 10 s minimum sitting-upright period) and will be covered in a nitrile sleeve and fully wrapped in waterproof dressing to allow participants to wear the device during bathing activities. Participants will keep a diary on their working days and working hours.

#### Biochemical variables

HbA1c and lipids (serum total cholesterol, HDL cholesterol and triglycerides) will be assessed using standard laboratory methodology.

The health benefits of reduced sedentary behaviour are likely mediated by several mechanisms. The results will, therefore, be weighed together in a clustered cardiometabolic risk score (CCMR) [33]. CCMR will be determined by summing *z*-scores ([value − mean]/standard deviation (SD)) of waist circumference (cm), mean arterial pressure (mmHg), HbA1c (mmol/mol), the inverse of HDL (mmol/L) and triglycerides (mmol/L), using sex-specific means and SDs based on previous studies [33, 34]. The use of a common mean and SD for standardized variables at two time points ensures that changes in the score can vary from zero. We will divide both by 5, separately, to account for the number of variables included. Change in the CCMR will be calculated by subtracting the follow-up CCMR from the baseline CCMR. Mean arterial pressure provides a better representation of the average pressure throughout a single cardiac cycle and will be used instead of systolic and diastolic blood pressure. Mean arterial pressure will be calculated using the formula (systolic pressure + [2 × diastolic pressure]/3) described as being one third of the distance between the systolic pressure and diastolic pressure [34].

#### Anthropometric data

Height and weight are measured without shoes, to the nearest 0.1 kg for body weight and to the nearest 0.1 cm for height. BMI is calculated as weight (kg)/height (meters^2^). The blood pressure will be measured after a 5–10-min rest, sitting on the chair with both feet on the floor and always in the same arm. The average of two readings are recorded for systolic and diastolic blood pressure. Waist circumference is measured in a standing position with a tape measure to the nearest 0.5 cm at the level midway between the lower rib margin and the iliac crest during a light exhale. Waist circumference is measured twice, and if there is a difference > 1 cm, the measurements are repeated; otherwise, a mean value is counted to the nearest 0.5 cm. The same measuring tape will be used during the whole study period.

#### Health-related quality of life

Health-related quality of life will be measured by the RAND-36 [25]. The Swedish translation of the RAND-36 is conceptually equivalent to the English version [26].

#### Fatigue

Fatigue will be measured using the four-item General Fatigue subscale of the Multidimensional Fatigue Inventory-20 (MFI-20) [27]. MFI-20 is a self-reporting and validated test, incl. the Swedish version [28]. MFI-20 is a 20-item multidimensional tool that uses a Likert-type scale from 1 to 5, with total scores with range 4–20. MFI-20 contains 5 subscales: General Fatigue, Physical Fatigue, Reduced Motivation, Reduced Activity and Mental Fatigue [27].

#### Musculoskeletal problems

A numerical rating scale (NRS) questionnaire will be used to measure pain intensity [29]. The scale has 11-points (i.e. 0–10) with 0 meaning ‘No pain’ and ‘10’ meaning ‘Pain as bad as you can imagine’, accompanied by the instructions ‘Please rate your pain by indicating the number that best describes your pain on average in the last 24 h is recommended as a core outcome measure in clinical trials of chronic pain treatments’.

#### Self-efficacy

Swedish translation of General Self-Efficacy scale (GSE-10) is used to assess the strength of an individual’s belief in his/her own ability to respond to difficult situations and to deal with setbacks [30].

#### Diet assessment

During the activity measurement week, the participants will keep a food diary of everything they eat and drink (excl. water) during three consecutive days (including one weekend day; Saturday or Sunday). The results are compiled using a programme for nutritional calculations (Dietist Net Pro).

### Plans to promote participant retention and complete follow-up {18b}

Participants are provided with a study calendar as a reminder of upcoming appointments and follow-up phone calls to promote participant retention and completion.

### Data management {19}

Study data will be collected and managed using REDCap electronic data capture tools hosted at Umeå University. REDCap is a secure, web-based software platform designed to support data capture for research studies. REDCap provides (1) an intuitive interface for validated data capture, (2) audit trails for tracking data manipulation and export procedures, (3) automated export procedures for seamless data downloads to common statistical packages and (4) procedures for data integration and interoperability with external sources [35, 36].

REDCap uses Electronical Case Report Forms (eCRF) which increases the compliance to the study protocol used by diabetes specialist nurse. REDCap directly notifies if any data is missing. The programme allows secure file uploading of activPAL data as well as records/diaries.

Scheduling function in eCRF makes it possible to schedule the telephone follow-up and if data is lacking, i.e. when it is time to make a follow-up telephone call and if participant is receiving the SMS text messages as planned.

### Confidentiality {27}

REDCap software ensures the secure data collection and maintenance both during and after the trial.

### Plans for collection, laboratory evaluation and storage of biological specimens for genetic or molecular analysis in this trial/future use {33}

No biological specimens obtained during the conduct of the trial will be stored for future use.

## Statistical methods

### Statistical methods for primary and secondary outcomes {20a}

Random effects mixed model analysis will be used to determine changes between the two study arms. The threshold for statistical significance will be set at *p* < 0.05. To avoid overestimating the impact of the intervention, an intention-to-treat approach will be adopted to evaluate the impact on the primary and secondary outcomes.

### Interim analyses {21b}

No interim analyses will be conducted as we do not foresee any potentially serious outcomes.

### Methods for additional analyses (e.g. subgroup analyses) {20b}

Self-efficacy is considered a potential moderator for behavioural interventions [21]. Therefore, analyses will be stratified based on self-efficacy level in a subgroup analysis.

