Interventions targeting specific workplaces have been designed to reduce occupational sedentary behaviour in order to reduce the risk of chronic diseases [15]. Pereira et al. found that a multilevel workplace intervention, including the use of sit-stand workstations, is effective for reducing sitting time over a period of 12 months [16]. Further, among participants with prediabetes or diabetes, a meaningful improvement in the clustered metabolic risk scores was noted [16]. However, there is still a paucity of evidence on workplace sedentary interventions targeting individuals with chronic diseases such as T2DM [3, 15, 17]. Furthermore, a 3-year trial showed that individual, biweekly counselling decreased sedentary time [18], but it may not be suitable for implementation in routine primary health care due to resource and personnel constraints.

Mobile health technologies (mHealth) could be used to support reduction in sedentary behaviour and to increase PA at low cost [19].The Global Observatory for eHealth (GOe) has defined mHealth as a medical and public health practice supported by mobile devices, such as mobile phones, patient monitoring and other wireless devices, and personal digital assistants [20]. Activity trackers often include functions that support individual goal setting and self-monitoring, which may enhance motivation and self-efficacy [21]. Importantly, some wrist-worn activity trackers alert the individual after a long bout of uninterrupted sitting and may help to reduce sitting time [19]. Short Message System (SMS) reminders may also facilitate behaviour change [20, 22, 23]. Person-centred care is a common feature of primary health care and involves tailoring treatment strategies to suit the individual [24]. Both activity tracker and SMS text reminders provide individual-level support and may lead to increased awareness of sedentary behaviour in people with T2DM [25].

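### Self-efficacy is to be assessed as an effect modifier, but the only method named is stratified analysis, which does not test whether the effect differs between levels (minor)

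*Protocol article*

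**What the plan says.** Under Other outcomes the aim is stated as "Self-efficacy will be evaluated as an effect modifier of changes in sitting time and steps". The section on additional analyses {20b} calls self-efficacy a potential moderator and draws from this that "analyses will be stratified based on self-efficacy level in a subgroup analysis". That is the only method given for the aim. Neither the cut-off nor the number of levels is stated.

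The section on statistical methods for primary and secondary outcomes {20a} specifies a random effects mixed model and a 0.05 significance threshold, without an arm-by-self-efficacy term. The Self-efficacy section names the GSE-10 as the instrument. No section of the article mentions an interaction test or any other comparison of the effect between self-efficacy levels.

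**The concern.** Effect modification is a statement about a contrast: the arm difference at one level of self-efficacy minus the arm difference at another. Analysing each level separately gives two arm differences, but no estimate, interval or test for that contrast. The method named therefore does not answer the question posed.

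The practical risk lies in what readers do with stratified results. If one level is significant and the other is not, it is tempting to conclude that the intervention works only in people with high (or low) self-efficacy. That pattern can arise easily when the effect is the same in both groups, because each stratum has far less power than the whole trial. The Discussion foresees use of the intervention in routine primary care, where such a claim could affect who is offered it.

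**Working it through.** **Inputs, all from the protocol article**
- Effect and SD: "Based on an increase of 1496 (standard deviation = 2930) steps/day after 3 months" (Sample size {14}).
- Size and power: "a total of 142 participants would have 80% power in finding a statistically significant difference in step count between the groups", with 15% dropout (same section), so 142 × 0.85 = 120.7 evaluable.
- Allocation 1:1 (Sequence generation {16a}).
- Significance level 0.05 ({20a}); two-sided is assumed, as sidedness is not stated.
- Assumed, because no split is given: two strata of equal size, with the same SD in each.

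**The plan's own figure**
- n per arm = 2 × (1.96 + 0.842)² × (2930/1496)² = 2 × 7.85 × 3.836 = 60.2.
- Total = 120.4, and 120.4/0.85 = 141.7, which rounds up to the stated 142. Rounding up to 61 per arm first gives 144.
- Power with 120.7 evaluable is 80.1%. The planning figures are consistent.

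**Power within a stratum, planned effect equal in both**
- Evaluable per stratum = 120.7/2 = 60.35.
- SE of the arm difference = 2930 × √(4/60.35) = 754.
- 1496/754 = 1.983, so power = Φ(1.983 − 1.96) = 50.9%. A t-test with 30 per arm gives 49.4%.

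**Chance that exactly one stratum is significant**
- The strata are independent, so the probability is 2 × 0.509 × 0.491 = 50.0%. Both are significant in 25.9% and neither in 24.1%.
- Without dropout (142 evaluable), power per stratum is 57.6% and exactly one is significant in 2 × 0.576 × 0.424 = 48.9%.
- Two unequal strata, from 40/60 to 20/80, give 50–63%.

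**Dependence on the true common effect (equal halves, range over 120.7 to 142 evaluable)**

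| True effect in both strata, steps/day | Exactly one stratum significant |
|---|---|
| 0 | 9.5% |
| 500 | 18–20% |
| 1000 | 39–42% |
| 1250 | 47–49% |
| 1496 | 49–50% |
| 2000 | 30–37% |
| 2500 | 10–16% |

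**The interaction test instead**
- SE of the difference between the two stratum effects = √2 × 754 = 1067.
- With equal true effects it rejects in 5.0% of trials, by construction and in a simulation of 2,000,000 trials.
- For a true between-stratum difference of 1496: 1496/1067 = 1.402, so power = Φ(1.402 − 1.96) = 29%. With 142 evaluable it is 33%.
- Difference detectable with 80% power = (1.96 + 0.842) × 1067, about 2990 steps/day, or twice the planned effect.

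**The case against.** The strongest reply is that the article does not say how the strata will be read. It nowhere states that modification will be inferred from which stratum crosses p < 0.05. Stratum estimates with confidence intervals, followed by a formal comparison, would also fit the sentence in {20b}. The article is condensed, and an analysis plan that is not shown could contain the interaction test. This stands as far as the 50% figure goes: it belongs to a reading rule that the protocol does not state. It does not remove the point, because the article names a method for a named aim, that method alone does not address the aim, and nothing in the text signals an accompanying test.

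A reader might also infer that participants could be stratified on a self-efficacy score already changed by treatment. The Background does say that tracker functions "support individual goal setting and self-monitoring, which may enhance motivation and self-efficacy", and neither passage on the analysis specifies the baseline score. The documents do not support this as a finding. A moderator ordinarily means a pre-treatment characteristic, the timeline figure is not available, and nothing states or implies the use of a follow-up score. It is silence, not an error.

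Cutting a score into levels is a common and readable choice, and a continuous interaction brings its own assumption of linearity. The preference for a continuous score is therefore secondary to having an interaction test at all.

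Finally, the analysis already sits among other outcomes and additional analyses, apart from the primary and secondary outcomes. That lowers its importance.

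**Conclusion.** The point holds in a limited form. The stated aim is effect modification, and the stratified analysis named for it provides no test of a difference in effect. Severity is minor, since no primary conclusion depends on this analysis.

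A reader might conclude that the plan will produce a spurious one-group-only result about half the time. That is too strong. The figure of about 50% needs three conditions together: a true effect near 1496 steps/day in both strata, two roughly equal strata, and modification read from stratum-specific p-values. The documents do not fix the second or the third. With a true common effect of 0–500 or about 2500 steps/day, the rate is about 10–20%.

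The calculation is for steps, because the article gives no effect or SD for total sitting time. It also uses a simple two-group comparison of means, which reproduces the plan's sample size, and not the repeated-measures model. Any outcome with about 80% overall power would behave in the same way.

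**What to change.** In {20b}, state that effect modification will be tested by the interaction of arm, time and baseline GSE-10 in the random effects mixed model fitted to all participants. Preferably enter GSE-10 as a continuous score and check linearity. Report the interaction estimate with its 95% confidence interval. Present arm differences by stratum, or at chosen percentiles of baseline GSE-10, with confidence intervals and as description only. Using the word baseline also settles which measurement is meant.

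The cost is a change of wording. The GSE-10 is already among the planned measures; that it is taken at baseline is an assumption here, because the timeline figure is not shown. The downside is an imprecise interaction estimate, with about 29% power for a between-stratum difference equal to the whole planned effect. The result should therefore be reported as exploratory, and a non-significant interaction should not be taken as evidence that the effect is uniform.
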